#### Home-based protocol

In addition to the twice-weekly, site-based exercise sessions, participants will be asked to include 30 minutes of walking at moderate intensity on the remaining five days each week when subjects do not complete the biweekly, in-person exercise sessions.

#### Assessment of aerobic capacity

Aerobic capacity will be measured at baseline and after 8 weeks of exercise using the six-minute walk test (6MWT). The 6MWT accurately estimates maximal oxygen uptake capacity (VO2max) using regression equations, including distance walked, sex, age, and body mass index [36].

#### Cognitive pulse assessments

Participants will complete twice-weekly, brief cognitive pulse assessments using a digital cognitive tool, which will take approximately 10–20 minutes to complete. These will occur immediately after each in-lab exercise session in a designated testing space, enabling the study team to capture near-term changes in cognitive function related to exercise. Additionally, participants will complete the full-length digital cognitive assessments at week 0 (baseline) and week 8 in a quiet testing room. These assessments will simulate real-world cognitive tasks and will yield high-resolution, domain-specific cognitive profiles.

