#### Biomarker collection strategy

Brain and cardiometabolic health will be assessed using a hybrid biospecimen collection protocol. Two venipuncture-based blood draws will be conducted through Quest Diagnostics, occurring at week 0 (pre-intervention) and week 8 (post-intervention) under standardized fasting conditions. To maximize participant safety and minimize all possible influences of acute exercise [20], pre-intervention blood draws will be obtained no later than 7 days prior to, but no sooner than 24 hours before, the initiation of the first exercise session, and post-intervention blood draws will be obtained within 24–48 hours after completion of the final exercise session. No blood draws will occur on the same day as in-lab exercise. For all participants, plasma samples will be assessed for cardiometabolic risk, which will include high-sensitivity C-reactive protein (hs-CRP), glycated hemoglobin (HbA1c), and fasting total cholesterol, high-density lipoproteins (HDL), low-density lipoproteins (LDL), triglycerides, insulin, and C-peptide levels, which will provide time-sensitive insight into the inflammatory, glycemic, lipid, and insulin resistance markers across the intervention period. Furthermore, the extent of AD-associated neuropathology will be assessed at baseline via plasma samples, which will include amyloid beta peptide 1–42 (Aß1–42), Aß1–40, Aß1–42/Aß1–40 ratio, and phosphorylated tau at threonine 217 (p-tau217). These biomarkers will be subsequently integrated into a single analytical interpretation of AD risk, which has an 88% positive and 91% negative concordance with amyloid-PET-based results [38]. The aforementioned biomarkers will serve as staging and stratification variables, enabling the utilization of such biomarkers as covariates or effect moderators (e.g., assessing whether intervention response differs by baseline pathology status) without presuming measurable longitudinal change over the short intervention window. Additionally, in order to capture biologically meaningful change over an 8-week duration, plasma neurofilament light chain (NfL) will be obtained and measured at baseline and at post-intervention. Unlike the amyloid- or tau-based biomarkers, NfL reflects ongoing neuroaxonal stress and overall neurodegeneration and has demonstrated sensitivity to behavioral and lifestyle interventions, including exercise- and sleep-related alterations, over relatively short time periods (e.g., 8 weeks) [39]. Consequently, NfL is more appropriate for detecting intervention-related biological signals within the timeframe of this pilot study.

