#### Cognitive pulse assessments

Full-length, digital cognitive assessments (approximately 20 minutes) will be conducted at week 0 and week 8 in a quiet testing room at the University of Miami or, if unable to complete in person, via a secure video conference with a trained research assistant or postdoctoral fellow. Throughout the study duration, participants in this group will also complete brief, twice-weekly cognitive pulse assessments in each participant's  own home setting using the Digital Neuro-Signature Platform cognitive tool on two mornings per week after wearing the Elemind Neuromodulation headband the night before.

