#### Protocol structure and considerations

To reduce participant burden and improve standardization, in-lab exercise sessions and cognitive assessments will follow the same cadence and structure as in the exercise-only arm: twice-weekly, 60-minute, supervised sessions that will focus on aerobic and resistance training, home-based walking program, and brief digital cognitive assessments (the Digital Neuro-Signature Platform) immediately after each session. Participants will also wear the Elemind Neuromodulation headband for at least 3–4 nights per week across the 8-week period, with an initial 7-day, passive, onboarding screening phase of wearing the headband nightly without stimulation in combination with wearing the Fitbit device continuously to establish baseline sleep patterns, physical activity levels, and ensure that all eligibility criteria are satisfied. Finally, subjects will also wear the Lys device continuously throughout the 8-week trial period.

To manage cumulative burden, scheduling flexibility will be emphasized. Although participants will be offered a choice of days and times for in-lab sessions to fit each participant’s weekly routines, morning times will be strongly encouraged across all participants, as prior work has suggested that older adults generally show better cognitive and exercise performance in the mornings [42, 43]; this will further improve standardization. Staff will work closely with participants to accommodate visit times and ensure ample time for recovery between activities. Weekly adherence and well-being check-ins will be conducted and documented to monitor fatigue, motivation, and adverse effects.

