#### Cognitive pulse assessments

As in the other arms, participants will complete brief, digital cognitive assessments biweekly during lab visits and full-length assessments at week 0 and week 8. For improved standardization, participants in this group will also be asked to attend in-person exercise sessions on the days after they wore the Elemind Neuromodulation headband the preceding night.

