#### Cognitive assessments

The augmented reality platform delivers a Digital Neuro-Signature (DNS) based on > 700 sensor-derived digital biomarkers captured through brief (10–20 minutes), gamified cognitive tasks that simulate real-world activities [63]. The DNS has demonstrated high sensitivity (≈ 0.91) and specificity (≈ 0.82) in detecting MCI and early AD progression as well as a predictive accuracy of approximately 94% for conversion risk to AD within aging cohorts in prior work [64]. A longitudinal validation study (*N* = 525) showed strong correlations with traditional neuropsychological tests, such as the Mini-Mental State Examination (MMSE) and Montreal Cognitive Assessment (MoCA), and showed that DNS outperformed conventional tools in detecting early cognitive change [64]. The augmented reality-based Cognitive Assessment Platform provides reliable, ecologically valid cognitive phenotyping suitable for remote, high-frequency, digital health studies.

The DNS cognitive assessments, which are suitable for both iPhone iOS and Android devices, are augmented reality technologies that test a participant’s cognitive and functional aptitude via a self-learning (machine learning) algorithm. Cognitive scores will be assessed during baseline and follow-up on site or, for those in the sleep-only intervention group who are physically unable to come on site, at the participants’ homes using an application on a smart device. Participants will be asked to perform tasks using virtual reality representations on each subject’s smartphone’s camera. Using movement and response data plugged into machine learning systems, the service will provide a validated measure of MCI/AD risk, which will be shared with the study team and participants through a computer dashboard and through the app, respectively. The app will test all cognitive domains, but the three following cognitive function outcome variables, which are particularly susceptible to decline in MCI, will be considered the primary cognitive outcomes of interest in this trial: (1) spatial memory, (2) prospective memory, and (3) executive function. All other cognitive functions will be considered secondary outcomes of interest. All data will be automatically transmitted to the study team on an encrypted dashboard. The DNS cognitive assessments have been validated in previous literature [65].

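### Pulse cognitive scores are not comparable between sleep-only and the two exercise arms, and the primary full-length test allows a change of test mode in sleep-only alone

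*Protocol article*

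**What the plan says.** **Pulse tests.** The Cognitive pulse assessments section for group 1 (exercise only) says: "These will occur immediately after each in-lab exercise session in a designated testing space". It gives the purpose as "enabling the study team to capture near-term changes in cognitive function related to exercise". For group 3 (combined), Protocol structure and considerations places "brief digital cognitive assessments (the Digital Neuro-Signature Platform) immediately after each session". For group 2 (sleep only), the pulses are taken in the participant's "own home setting using the Digital Neuro-Signature Platform cognitive tool", "on two mornings per week after wearing the Elemind Neuromodulation headband the night before". The group 3 Cognitive pulse assessments section nevertheless says: "As in the other arms, participants will complete brief, digital cognitive assessments biweekly during lab visits".

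**Use of the pulses.** Baseline and follow-up visits names the biweekly data, alongside baseline and week 8, among the data used to assess change in cognition. No between-arm analysis of pulse scores is described.

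**Full-length test.** This is done at weeks 0 and 8 and supplies the primary cognitive outcome. For exercise-only it is in a quiet testing room. The group 2 section allows a video alternative, and Cognitive assessments (under Measures and instruments) limits home testing to "for those in the sleep-only intervention group who are physically unable to come on site".

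**Model.** The Analysis plan fits mixed models with time at baseline and 8 weeks only, and takes group × time as the main efficacy test. The covariates listed under Adherence and engagement include no term for test mode or setting.

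**Blood draws, for comparison.** The group 1 Biomarker collection strategy says "post-intervention blood draws will be obtained within 24–48 hours after completion of the final exercise session", to limit acute exercise effects.

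**The concern.** A cognitive score taken minutes after a 60-minute session reflects the participant's state at that moment as well as any lasting effect of the programme. A score taken at home on a quiet morning does not carry the same acute component. When these conditions follow the arm exactly, a difference between arms cannot be attributed to the intervention, and no covariate can repair this because the arms do not overlap. The article treats acute exercise as a nuisance for blood markers and plans around it there.

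The full-length test raises a separate and narrower issue. A remote alternative open to one arm lets test mode change between week 0 and week 8 in that arm only, and a group × time interaction would pick that up.

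The trial is meant to supply effect sizes for a later, fully powered trial, so a distortion in either measure would carry forward into that design.

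**Working it through.** The plan states no figure on this point, so there is none to reproduce. The check compares conditions by arm and then sizes the possible effect under stated assumptions.

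**1. Conditions by arm**

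| | Exercise-only | Combined | Sleep-only |
|---|---|---|---|
| Pulse setting | Lab | Lab | Home |
| Pulse timing | Right after session | Right after session (attendance requested the day after a headband night) | Morning after a headband night |
| Remote full-length test | Not stated | Not stated | Allowed if unable to attend |

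Pulses per participant: 2 per week × 8 weeks = 16. With full attendance, 16 of 16 are post-session in each exercise arm and 0 of 16 in sleep-only. Exercise-only and combined match on setting and post-session timing. They differ in the headband night, which is part of the combined intervention.

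**2. Does the pulse problem reach the primary test?** Time in the primary model has two levels, baseline and week 8, both from full-length tests. On the stated plan, pulse scores do not enter it.

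**3. Size for a pulse contrast.** The article gives no acute or setting effect, so a shift *a* of 0.1–0.5 SD in both exercise arms is assumed, with no true intervention difference. For a three-arm F test with 20 per arm (df 2, 57; α = 0.05), the arm means are (*a*, 0, *a*) and the noncentrality is 20 × Σ(μᵢ − μ̄)² = 20 × (2/3)*a*² = 13.33*a*².

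- *a* = 0.1: noncentrality 0.133, rejects about 6%
- *a* = 0.2: 0.533, about 9%
- *a* = 0.3: 1.20, about 15%
- *a* = 0.5: 3.33, about 34%

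The nominal rate is 5%.

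**4. Size for the full-length test.** Let a share *q* of sleep-only be remote at week 8 but on site at week 0, with mode effect *b* (SD units of the analysed change). The bias in the sleep-only mean change is *q* × *b*.

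- Low end: 0.10 × 0.2 = 0.02 SD (2 of 20 participants switch)
- High end: 0.50 × 0.5 = 0.25 SD (10 of 20 switch)

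Over this range the F test rejects about 5–11% of the time with no true difference.

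If a participant is remote at both visits, a constant effect cancels: (y₈ + b) − (y₀ + b) = y₈ − y₀.

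**5. Scale.** The standard error of a 20 versus 20 difference is √(2/20) = 0.316 SD, and the 95% half-width is about 0.64 SD.

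**The case against.** The strongest reply has four parts.

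- **The pulses are outside the efficacy model.** This stands. A reader might infer that all between-arm cognitive differences, including the primary one, mix acute exercise with the intervention effect. The documents do not support that, because the primary model uses only the full-length tests and nothing places those tests straight after a session. The article does not say how long after the last session the week-8 test falls, so carry-over is possible but not shown. A reader might also infer that every pulse contrast is confounded, but exercise-only versus combined shares setting and post-session timing.
- **Post-session timing is deliberate.** This also stands. Moving the pulses before the session would give up a measurement that the article names as its aim. The answer is therefore to restrict how these scores are compared and leave their timing alone.
- **Remote testing is an exception for those who cannot attend.** This is fair. The 20 sleep-only participants are a ceiling, the expected number is not given, and most of the assumed range is small against a 0.64 SD half-width.
- **An article may leave mode rules and visit windows to the full protocol.** This is accepted, so their absence is not the finding. The finding rests on what is stated: a remote option described for one arm only on a primary outcome, different pulse conditions by arm, and two sections that disagree on where sleep-only pulses are taken.

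**Conclusion.** The point holds in a limited form.

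- **Pulse scores** are not comparable between sleep-only and either exercise arm, although the article counts them among the data for assessing cognitive change. With an assumed shift of 0.1–0.5 SD, a three-arm comparison would reject about 6–34% of the time with no intervention difference. Exercise-only versus combined is not affected by setting or post-session timing.
- **The primary group × time test** is exposed only through the remote option stated for sleep-only, and only for participants who change mode between visits. Under assumed switching of 10–50% and a mode effect of 0.2–0.5 SD, the bias is 0.02–0.25 SD, in a direction that cannot be predicted. The article gives neither input.
- **The group 3 statement** that pulses take place in lab visits as in the other arms contradicts the group 2 section and must be reconciled with it, whatever view is taken of the bias.

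**What to change.** 1. **Full-length test mode.** Require the same mode, site or remote, at weeks 0 and 8 for each participant. Make the remote option available on the same terms in all arms, record the mode used, and add a sensitivity analysis that excludes or adjusts for participants who switched.
2. **Pulse scores.** State that post-session pulses are a within-arm outcome, or are compared only between exercise-only and combined, and are not used in contrasts with sleep-only.
3. **Week-8 full-length test.** Schedule it on a day without an in-lab session and before any walking that day, in line with the separation already made for blood draws.
4. **Wording.** Reconcile the group 3 and group 2 Cognitive pulse assessments sections on where sleep-only pulses are taken.

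**Cost.** The changes need protocol wording, one recorded variable and minor scheduling constraints. Blood is drawn at a Quest Diagnostics location and not at the study site, so item 3 may add one separate site attendance. Pulse contrasts with sleep-only are given up. The acute post-exercise measurement is kept.

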#### Baseline and follow-up visits

Data will be collected at baseline, biweekly, and at the 8-week follow-up to assess changes in sleep, exercise, biomarkers, and cognition. After consent and randomization, participants will be onboarded in person to each intervention-specific device and observed for a 7-day period prior to the baseline visit to establish baseline sleep patterns and/or physical activity levels relevant for each assigned intervention and to ensure all eligibility criteria are satisfied. Cognitive function will be measured using an augmented reality-based tool at baseline and week 8, with brief pulse assessments administered twice-weekly throughout the intervening period. Blood biomarkers will be collected via venipuncture at Quest Diagnostics (baseline and week 8). Physical activity and sleep data will be respectively monitored using Fitbit (all groups) and the Elemind headband (sleep and sleep + exercise groups), and light exposure will be tracked via the Lys device (sleep and sleep + exercise groups). Participants will also complete validated self-report surveys (e.g., PASE, CHAMPS–MET, PROMIS instruments) to capture psychosocial and behavioral variables at weeks 0 and 8. This multimodal approach will enable temporally-aligned, comprehensive data capture across digital and self-reported domains (see Table 3).

**Table 3 Tab3:** Timeline of questionnaires provided

Variable	Screening	Baseline	8-week
Basic Info Screening Form (eligibility criteria)	X		
Physical Activity Readiness Questionnaire (PAR-Q)	X		
Quick Mild Cognitive Impairment screen (QMCI), 6-item	X		
Demographic Questionnaire		X	
Chronic Health Questionnaire		X	X
PROMIS Self-reported Cognitive Functioning Behaviors Short Form		X	X
PROMIS Sleep Disturbance 4a		X	X
PROMIS Emotional Support 4a short form		X	X
PROMIS Depression 4a shot form		X	X
PROMIS Anxiety 4a short form		X	X
PROMIS Social Isolation 4a		X	X
General PROMIS Life Satisfaction 5a		X	
Cross Ethnic-Racial Identity Scale		X	
PASE Physical Activity Questionnaire (exercise and sleep + exercise interventions only)		X	X
CHAMPS-MET Physical Activity Questionnaire (exercise and sleep + exercise interventions only)		X	X

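### In the two exercise arms every pulse test follows a session, so the pulses cannot show the near-term, session-linked cognitive change that the protocol says this timing will capture

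*Protocol article*

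**What the plan says.** For the exercise-only arm, the protocol article (Interventional group 1, Cognitive pulse assessments) fixes the timing of the pulses: "These will occur immediately after each in-lab exercise session in a designated testing space". It gives the reason in the same sentence: "enabling the study team to capture near-term changes in cognitive function related to exercise".

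For the combined arm, Interventional group 3, Protocol structure and considerations, repeats the timing: "brief digital cognitive assessments (the Digital Neuro-Signature Platform) immediately after each session". The Cognitive pulse assessments section for that arm adds that participants will be "asked to attend in-person exercise sessions on the days after they wore the Elemind Neuromodulation headband the preceding night".

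Baseline and follow-up visits places the pulses between the two main assessments, "with brief pulse assessments administered twice-weekly throughout the intervening period", so there is no baseline pulse. The other cognitive measurements are the long tests: "participants will complete the full-length digital cognitive assessments at week 0 (baseline) and week 8 in a quiet testing room".

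In the sleep-only arm the pulses are done at home, "on two mornings per week after wearing the Elemind Neuromodulation headband the night before". The protocol does not say there that they will capture near-term change.

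**The concern.** A near-term change related to exercise, measured straight after a session, needs a reference: the same person, on the same test, without a session just before it. The schedule for the two exercise arms contains no such reading. No pulse is placed before a session, on a non-session day or at baseline.

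The trial is meant to yield signals and mechanistic insight for a larger study. A rise in pulse scores over eight weeks could come from repeated testing or from accumulated training. With no reference reading, such a rise could be reported as a session effect that the data cannot support. Each participant takes about 16 tests of 10 to 20 minutes, so the data collection is substantial. An analysis plan cannot repair this, because the timing of the tests decides which data will exist.

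**Working it through.** The protocol states no power or precision for the pulses, so there is no figure to reproduce. The check has two parts: whether the effect can be estimated as scheduled, and what precision the same number of tests would give if rearranged.

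**Inputs**
- Pulses per participant: 2 per week × 8 weeks = 16 (Baseline and follow-up visits).
- Participants: 20 per arm, so 40 in the two exercise arms (Participant recruitment).
- Timing and setting: exercise-only and combined after a session in the lab; sleep-only at home (the three group sections).

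**1. Within person, as scheduled.** Write pulse j of person i as

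y_ij = a_i + c·week_ij + b·S_ij + e_ij,

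where S = 1 if the test follows a session. In the exercise arms S_ij = 1 for all 16 pulses. Only the sum a_i + b appears in the data, so b cannot be separated from the person's level. A rank check of the design matrix (20 per arm, person intercepts, arm-specific weekly trends) agrees: removing the session column does not lower the rank, so b is not identifiable.

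**2. Between arms.** Sleep-only pulses follow no in-lab session and might serve as the reference. But S = 1 exactly where the test is in the lab, and S = 0 exactly where it is at home. Once a setting term is allowed, b is again not identifiable. Without that term it can be computed, but it then absorbs the home-versus-lab difference and any accumulated training.

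**3. Adding the full-length tests at weeks 0 and 8.** These are not tied to a session, but they are a different form from the pulse. With a term for form, b becomes estimable only if home and lab testing are assumed equivalent and the form difference is the same in all arms. With a setting term as well, b is again not identifiable.

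**4. Same 16 tests, 8 before and 8 after a session.** Let σw be the within-person SD of a pulse score.
- Standard error of one person's difference: σw × √(1/8 + 1/8) = 0.5 σw.
- 95% half-width, 20 people: 1.96 × 0.5 / √20 = 0.219 σw.
- 95% half-width, 40 people: 1.96 × 0.5 / √40 = 0.155 σw (0.15 to two decimals, from 0.1550 rounded down).

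These assume independent errors, no missed sessions and the same effect in everyone. If the effect varied between people with an SD of 0.5 σw (an assumption for illustration), the half-width for 20 people would be 1.96 × √(0.25 + 0.25) / √20 = 0.31 σw.

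**The case against.** The strongest reply is that the phrase need not mean the acute effect of a session. It could mean change from week to week during training, ahead of the week 8 test, and the pulses do give such trajectories. Associations with session heart rate also remain estimable, and the combined arm's Analysis strategy plans dose-response work of that kind. This stands in part: the pulses are not uninformative. But the protocol ties the phrase to testing immediately after each session, and a trajectory or dose association is not a change from before to after a session.

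A second reply is that little hangs on it. No objective or hypothesis names the pulses, the listed primary outcomes do not single them out, and the efficacy model uses only baseline and week 8. This stands, and it limits the weight of the point.

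A reader might also extend the point to the headband, because every sleep-only pulse follows a headband night and the combined arm's sessions are requested on such days. The documents do not support that extension. The promise of near-term change is made only for exercise, and the combined arm's request is explained as standardisation. Combined versus exercise-only is also a same-setting contrast for the headband, although it mixes acute and cumulative effects. Moving sleep-only pulses to mornings after nights without the headband would rely on nights that participants choose themselves. It would also lose the preceding night's headband sleep data, which that arm's Temporal synchronization section aims to link with cognition.

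**Conclusion.** The point holds for the exercise-only and combined arms. The pulses cannot separate a session's near-term effect from the person's own level, practice, accumulated training or lab setting, so the stated purpose of the post-session timing is not met. As scheduled there are 16 post-session pulses and no pre-session pulse per person, and the within-person contrast has no estimate. Rearranging the same tests would give about ±0.22 σw in one arm and ±0.15 σw across both, under the assumptions stated with the calculation.

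A reader might infer that the pulses are useless or that the efficacy comparison is damaged. Neither follows. Trajectories and dose associations remain estimable, and the group × time test on weeks 0 and 8 does not depend on the pulses. This is a change that should be made, in an exploratory part of the trial.

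**What to change.** In the exercise-only and combined arms, keep two pulses a week. Take one before a session and one after a session, with the order randomised or alternated across weeks. Analyse the within-person pre/post difference, adjusted for test number so that practice does not enter the contrast. Leave the sleep-only pulse schedule as it is.

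The cost is a change to protocol wording and scheduling. The number of tests, visits and staff stays the same, and participants already attend twice a week. The downside is half as many post-session readings, which makes any description of post-session trajectories less precise.

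If the schedule has to stay, restrict the statement in Interventional group 1, Cognitive pulse assessments, to week-to-week trajectories, and state that the pulses will not be interpreted as showing a session effect. This needs only a wording change.
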